### 3.7 What is the proposed duration of treatment (see interventions)

### 3.9 and 3.10. What are the proposed outcome measures, frequency and duration of follow-up?

- **Primary: Episodes of ILI and RTI, their duration and transmission in families.:** *We hypothesize that the intervention will reduce the number of episodes (by reducing transmission) and hence the number of days with symptoms.* During the feasibility phase we will pilot the use of both paper and web versions of illness diaries, and of monthly questionnaires (both web and paper based) with emailed reminders. Our preference is that index patients will be prompted by email to log onto the website monthly to complete questionnaires about illnesses during the last month since the duration of symptoms can be remembered reliably over a period of a few weeks. However those that prefer will be provided with a double sided A4 sheet (and spare sheets in case of families with frequent infections) to provide simple summary diary entries of respiratory tract infection, and will still get the monthly email prompt reminders. For each episode the index person will document: the nature of the infection; the duration of symptoms rated moderately bad (which we have shown is the most likely to be sensitive to change for individuals with cough and fever and can be remembered reliably over a period of a few weeks); the number of days where work/normal activities were impaired; whether other family members either had a similar infection before or after the index case, and what the time interval was; whether contact with the health service was needed; and (for the intervention group only) how well the index patient and other family members complied with the target behaviours. We have used diary sheets in our respiratory studies and found good levels of compliance. The monthly illness information will be supplemented by a questionnaire at the end of the winter (April) documenting the summary information, and which can be validated against the monthly information. We are currently using a similar end of winter questionnaire in a study of respiratory and ear infections in families (the 'PIPO' study <http://www.controlled-trials.com/ISRCTN53286030>), and shown it to be feasible and reliable; this questionnaire will particularly provide some information for those individuals not returning their diary or monthly questionnaires. Our experience with questionnaires is supported by illness transmission studies where similar questionnaires/diaries have been used. An illness will be classified based on the records as a potential ILI based on reported fever (or measured temperature >37.5), plus a respiratory symptom (sore throat, cough, coryza) plus a systemic symptom (prostration, headache, severe fatigue, severe muscle aches, severe malaise) i.e. using an analogous definition to the diagnostic sub-study. We will base our definition of RTI on consensus definitions developed in previous studies - which have defined a respiratory tract infection as 2 symptoms of an RTI for at least 1 day or 1 symptom for 2 consecutive days. Evidence of transmission will be defined as a respiratory illness developing within a week of another family member (viral shedding occurs mostly in the 5 days after symptoms commence and the average incubation period is 2 days). We will assess the implications of using different cut-offs in defining both symptomatic RTIs and the time defining transmission of RTIs.

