- **Diagnostic substudy.** This study will assess the extent to which ILI report by participants is laboratory confirmed influenza (based on pharyngeal samples transported in viral transport medium). This will allow some explanatory information for the trial results (transmission according to the type of viral illness); assessment of the generalisability of the results; and information to assess diagnostic spectrum bias. There is no widely accepted definition of influenza like illness but most definitions have a combination of fever plus other respiratory or systemic symptoms. Based on RCGP weekly sentinel practice returns we will inform all patients who have agreed to the virological study to commence this substudy when influenza virus is circulating in the community. This is necessary since we already know that the predictive values will be poor when influenza is not circulating. Patients with fever of >37.5, plus a respiratory symptom (sore throat, cough, coryza) plus a systemic symptom (chills, prostration, headache, severe fatigue, severe muscle aches, severe malaise) will record the range of symptoms and temperature twice daily (using tempadot thermometers) for at least 5 days; the symptoms recorded will be based on previous clinical studies in influenza and respiratory infections. We have used similar diaries successfully. Patients will be instructed to take their own viral samples using the simplest method possible: our provisional proposal is to do this by gargling with tap water into a universal container ([name] lab have recently shown this method to provide valid PCR results compared to conventional naso-pharyngeal swabs and transport media (unpublished data)). The validity of this can be confirmed during the pilot phase, and nasopharyngeal swabs will be used as necessary; the feasibility phase will also explore how much written and/or telephone support is needed for patients to take and send their own samples. Virological samples will be posted first class to [name] laboratory (Glasgow) to facilitate standard analysis using PCR to assess the presence of influenza and other respiratory viruses (Influenza A, B, C; Paraflu 1, 2, 3, 4; Coronaviruses; RSV; HMPV (human metapneumovirus); Adenovirus; Bocavirus). Patients will be asked both for the last episode of ILI and the last respiratory infection whether they contacted the doctor (or NHS Direct); and will be asked at the end of the diary whether for this episode they have contacted the doctor (or NHS Direct). The patients participating in this study will also be asked whether they would be prepared to provide similar samples and clinical information should a pandemic occur: having a network of patients in the community already experienced and able to provide clinical forms and samples at short notice could be invaluable in providing information about the clinical presentations during a pandemic; a series of practices with many patients in each area will complement the information generated from the MRC flu watch study (which is collecting information from fewer patients in each practice and over a much wider area).

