
**3.12 What is the proposed sample size?: Transmission of ILI.** All calculations are based on the patient randomised (the index person). We assume that our more rigorously developed, interactive, and tailored intervention will have an NNT of at least 25 and an OR of 0.76 - very slightly better than the previous booklets which had none of these features (OR 0.80, NNT 25). There are other reasons to assume this is a reasonable (if not conservative) effect size: people who have attended with respiratory infections are slightly more likely to be interested in participating, and in this group the effect size from previous study was significantly larger; a 20% reduction in transmission is the effect size seen in most of the studies of handwashing alone; a larger effect on behaviour is also likely given the heightened public concern about ILI since the above studies. If 10% suffer ILI (<http://www.eurosurveillance.org/em/v10n12/1012-223.asp>; <http://www.niaid.nih.gov/factsheets/flu.htm>), the average household size is 2.4 individuals (<http://www.statistics.gov.uk>) i.e. 24% can be affected by the transmission of ILI either to or from the index patient, and 20% of those with no intervention will develop ILI, then 15,074 patients are needed (assuming two-sided significance level of 5% and 80% power), or 16,000 to allow some leeway in assumptions (see table below). **Transmission of RTIs.** 16000 will have greater power to detect transmission of all RTIs, and for continuous outcomes this sample size will be extremely powerful (see table). **Nested diagnostic study.** We assume that: at least 10% of the index trial cohort will report ILI, i.e. approximately 1600; 50% will agree to the virological sub study (n=800) (based on the numbers agreeing to more intensive investigation in a current microbiological study of URTI in our group); flu virus is isolated in at least 50% of individuals presenting with ILI when ILI is circulating; and that 30-50% of patients are likely to contact the doctor then in the cohort reporting ILI then we should be able to estimate the positive predictive value of a clinical diagnosis in predicting laboratory confirmed influenza with 95% confidence intervals of +/- 10% in both the sample attending the doctor (n=240-400) and the sample not attending (n=400-560). For the analysis of the likely positive and negative predictive values (of symptoms, temperature) at each stage in the illness (12hours,24hours,36 hours etc) we will have greater precision since we can use the whole sample who agree to the diagnostic study.

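### The trial's ILI rule and the diagnostic sub-study's entry rule overlap but differ, so the sub-study's predictive value leaves out trial ILI counted on reported fever alone

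*Protocol*

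**What the plan says.** Protocol section 3.9 and 3.10 gives two ILI rules.

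- **Primary outcome.** The rule for classifying a trial illness reads: "based on reported fever (or measured temperature >37.5), plus a respiratory symptom (sore throat, cough, coryza) plus a systemic symptom (prostration, headache, severe fatigue". Two more items, muscle aches and malaise if severe, complete its systemic list. The protocol describes this as "i.e. using an analogous definition to the diagnostic sub-study".
- **Diagnostic substudy.** The patients who keep the twice-daily symptom and temperature diary are described thus: "Patients with fever of >37.5, plus a respiratory symptom (sore throat, cough, coryza) plus a systemic symptom (chills, prostration, headache, severe fatigue". The same two items complete the list.

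The sub-study paragraph states its aim as "This study will assess the extent to which ILI report by participants is laboratory confirmed influenza". Among its uses it lists help in interpreting the trial: "This will allow some explanatory information for the trial results (transmission according to the type of viral illness". Section 3.12 (nested diagnostic study) takes its numbers from everyone in the cohort who reports ILI: "at least 10% of the index trial cohort will report ILI, i.e. approximately 1600". Half of these are expected to agree to virology.

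**The concern.** The stated aim and the sample size both refer to ILI as participants report it, which is the population the primary-outcome rule classifies. The entry rule describes a different, overlapping population. An illness with reported fever and no reading above 37.5 counts fully in the trial's ILI outcome but does not meet the sub-study rule, so no virology is planned for it. No later analysis can recover it.

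At stake is the share of the trial's ILI that was really influenza, and hence how the transmission results are read by virus type and how far they generalise. Predictive values are also the subject of the second principal research question (section 2.2).

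**Working it through.** **1. The two rules side by side (section 3.9 and 3.10)**

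| Element | Trial ILI | Sub-study entry |
|---|---|---|
| Fever | reported fever is enough; measured >37.5 is an alternative | >37.5 only |
| Respiratory symptom | sore throat, cough, coryza | the same |
| Systemic symptom | five items, chills absent | the same five plus chills |

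**2. Who falls where**

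- Temperature 37.8, cough, headache: meets both rules.
- Reported fever with no reading above 37.5, cough, headache: trial ILI, outside the sub-study.
- Temperature 37.8, cough, chills as the only systemic symptom: in the sub-study, not a trial ILI.

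Neither rule contains the other. The third group can be removed at analysis, because the sub-study diary records the range of symptoms. The second group cannot be added back.

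**3. The plan's own counts (section 3.12)**

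- 16,000 x 10% = 1600 reporting ILI; 1600 x 50% = 800 in the sub-study.
- 800 x 30-50% = 240-400 contacting the doctor; 800 x 50-70% = 400-560 not doing so.

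All reproduce. None is reduced for illnesses that do not exceed 37.5.

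**4. Precision**

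The 95% half-width is 1.96 x sqrt(p(1-p)/n). At p = 0.5 it is 6.3% for n = 240, 4.9% for n = 400 and 4.1% for n = 560. The stated +/-10% needs n = 97.

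Let f be the share of reported ILIs that meet the >37.5 rule. The documents do not give f. For the smallest planned group, n = 240 x f:

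| f | n | half-width |
|---|---|---|
| 0.9 | 216 | 6.7% |
| 0.7 | 168 | 7.6% |
| 0.6 | 144 | 8.2% |
| 0.5 | 120 | 8.9% |
| 0.3 | 72 | 11.5% |

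The limit is f = 97/240, about 0.40. Any other loss, such as ILI arising when influenza is not circulating, draws on the same margin.

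**5. Which population the PPV describes**

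Let m be the PPV in trial ILI with measured fever >37.5, and q the PPV in reported-fever-only ILI. Leaving chills-only entrants aside:

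- PPV for trial ILI = f x m + (1 - f) x q
- Sub-study PPV minus trial PPV = (1 - f) x (m - q)

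Section 2.13 says the probability of influenza increases with fever, which points to q below m and a positive difference. The documents give none of f, m or q. The 50% in section 3.12 is a lower bound for people presenting with ILI, not for the >37.5 subset.

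Purely to show how the result moves, assume m = 0.50 and q from 0.10 to 0.50. Trial PPV is then 46-50% at f = 0.9, 38-50% at f = 0.7 and 30-50% at f = 0.5. These are not estimates.

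**The case against.** **The protocol claims only analogy.** It speaks of a potential ILI and does not say the rules are identical. The respiratory list and five systemic items match, and measured-fever cases qualify under both. This stands. A reader might infer that the PPV does not apply to the trial's ILI at all, and that goes too far: it applies to the measured-fever part.

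**The fever difference may follow from how data are collected.** Trial ILI comes from monthly questionnaires or summary sheets, where a reading may be missing; sub-study patients use thermometers. Section 2.13 also suggests harder signs, such as level of fever, to keep predictive value under spectrum change. This is a fair reason for recording temperature and reporting a measured-fever subset. It does not require leaving the other illnesses unsampled, and the protocol does not give it as the reason for the different rule.

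**Sampling may be wider than the diary rule.** The threshold grammatically governs who keeps the diary; the sentence on taking samples sets no trigger of its own, and section 3.4 has the diary completed when an ILI develops. The usual reading is that samples follow the diary rule, but the text leaves room for doubt. That is a further reason to reconcile it.

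**Explaining the trial result is one use among several.** This is true. The randomised comparison applies one ILI rule to both arms and does not depend on the PPV.

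**One rule would still not give a PPV for all trial ILI.** Sampling runs only while influenza circulates, a limit the protocol states and justifies but does not place on the trial outcome. This stands and belongs in the fix.

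**Conclusion.** The point holds in limited form. The two rules differ on fever and on chills, and the sub-study's aim and sizing assume the trial's population while its entry rule describes another. As written, the PPV leaves out reported-fever-only trial ILI. It is likely too high for trial ILI as a whole. That direction rests on the statement about fever in section 2.13; the documents support no figure for its size.

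Three stronger readings are not supported:

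- **The sub-study rule is simply stricter.** It is stricter on fever but wider on chills.
- **The overstatement has a known number of points.** Any such number comes from assumed values of f, m and q.
- **The sub-study becomes too small.** Its stated precision survives unless f falls below about 0.40, taking p = 0.5 and the smallest planned group of 240.

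The primary treatment comparison is not affected. The matter is still worth settling before recruitment, because illnesses that are not sampled cannot be recovered.

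**What to change.** Reconcile the primary-outcome and diagnostic-substudy paragraphs of section 3.9 and 3.10 to one ILI rule, used both to classify trial illnesses and to start the sub-study diary and sample:

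- reported fever or measured temperature above 37.5;
- one identical systemic-symptom list, with chills in both places or in neither;
- temperature recorded as a predictor rather than used as an entry condition;
- PPV reported for the trial definition, and separately for the measured >37.5 subset;
- a statement that both PPVs apply only while influenza is circulating.

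The cost is a change of wording in two paragraphs and in the participant instructions, plus somewhat more samples than under the stricter rule. These stay within the 800 already planned, since that number was derived from all reported ILI. Nothing is lost, because the measured-fever result can still be reported. If chills are added to the trial list, the primary-outcome classification widens slightly, so the choice should be made before data collection begins.

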**Target behaviours.** The intervention will encourage the use of regular handwashing throughout the winter months using normal soap or alcohol based handgel both within the family and in other settings. Then when somebody in the household has developed an ILI or other RTI (defined below), the aim is to influence the following behaviours: 'hygiene' in the index case and among family members- handwashing with soap or alcohol gel before any food eaten and after any skin or clothes contact with index case; three times daily washing of kitchen work/dining surfaces using a normal household cleaner; covering mouth when coughing (also see mask wearing, but mask wearing in non-pandemic years may not be acceptable or possible); minimising skin contact with family members, using disposable tissues, using separate towels and physical distancing where possible (more than 3 ft distance; minimising time in the same room; living/sleeping in separate rooms/bedrooms where possible). Wearing masks by the patient and family when in the same room as those with influenza (using FFP2, FFP3, N95 or equivalent masks) may limit the spread of large droplets by coughing; but it is the least likely behaviour to be acceptable in inter-pandemic years; our qualitative study will indicate how acceptable mask wearing is likely to be and inform whether masks are provided in the main trial. Based on the literature to date the key behaviour which has the most evidence is handwashing, and so this will be emphasised, but the website will help patients to develop individualised action plans based on their circumstances. Although a development phase cannot realistically determine with any power the effectiveness of each component of behaviour change in modifying transmission, in the analysis of the main trial we will be able to explore this. A development phase will nevertheless be able to provide some insight into the effectiveness of the different behaviours; development is also necessary for a complex intervention to allow us to understand and model the key factors determining the likely implementation of these behaviours ([http://www.mrc.ac.uk/pdf-mrc\\_cpr.pdf](http://www.mrc.ac.uk/pdf-mrc_cpr.pdf)):

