| 20% vs 17% (NNT 33; OR 0.82)                                                                                              | 2629                                                                                                                      | 27,386                                                                                                                                       | 6574                                                                                                                                  |
| 20% vs 16% (NNT 25 OR 0.76)                                                                                        | 1447                                                                                                                      | 15,074                                                                                                                                | 3618                                                                                                                                  |
| 20% vs 15% (NNT 20 OR 0.71)                                                                                               | 906                                                                                                                       | 9,438                                                                                                                                        | 2266                                                                                                                                  |
| Continuous outcomes e.g. days illness
(alpha=0.01 (multiple outcomes); beta=0.1)
standardised effect sizes |                                                                                                                           |                                                                                                                                              |                                                                                                                                       |

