**Main trial analysis.** The data will be analysed according to the Statistical Analysis Plan which will be approved by the Trial Steering Committee before the commencement of any analysis. One intention to treat analysis will be performed. We will assess the transmission of ILI or other respiratory tract infection - i.e. either between the index case and family members or from family members to the index person - using multiple logistic regression, the duration of symptoms labelled moderately bad days using multiple linear regression, and attendance at the GP surgery using Poisson regression, controlling for stratifiers. We found in our previous trial of leaflets there were no significant clustering effects by practice; our analysis will be based on the index patient to avoid a design effect due to family clustering. For the symptom data the main analysis will be of symptoms in the index person but a secondary analysis will assess symptoms reported for all other family members averaged at the level of the family. Confidence intervals will be reported, and the study will be reported in accordance with the CONSORT statement.

**Subgroup analysis (using two sided 1% significance levels).** We will assess whether any of the stratification variables are effect modifiers; whether age, deprivation, education level, and co-morbidities predict outcomes or are effect modifiers; whether self reported adherence to each behaviour determines outcome.

**Diagnostic study analysis.** We will assess the sensitivity specificity likelihood ratios and positive and negative predictive values for symptoms and temperature in the whole sample, and in the sub-samples who would not contact their practice or NHS Direct (either in this or in past episodes). We will use logistic regression to determine which symptoms (and or temperature) individually or in combination are most predictive. We will also estimate the predictive value of symptoms (and or temperature) for laboratory diagnosed influenza at 12 hours after the start of the illness, then at 24 hours, 36 hours, 48 hours, and 48+ hours.

**3.20 Has a pilot study been carried out?** We have not piloted this precise protocol, but have recruited very similar trial cohorts using similar recruitment mechanisms, and have developed similar websites

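### The 80% power for ILI transmission belongs to the 24% of index persons with an ILI in the household, not to the intention-to-treat set; on the protocol's own rates that set has about 76% at 16,000

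*Protocol*

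**What the plan says.** Section 3.12 of the protocol takes a 10% ILI incidence and an average household of 2.4 people, and multiplies them to reach the share of index persons for whom ILI transmission can occur: "24% can be affected by the transmission of ILI either to or from the index patient, and 20% of those with no intervention" go on to develop ILI. The target row of the effect-size table is "20% vs 16% (NNT 25 OR 0.76"), with 1,447 per group. The column heading says that these are people with complete outcomes for whom transmission to or from the index person is possible. The conclusion is: "then 15,074 patients are needed (assuming two-sided significance level of 5% and 80% power), or 16,000 to allow some leeway in assumptions".

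The main trial analysis (sections 3.17-.18) states: "One intention to treat analysis will be performed". Transmission is to be modelled by logistic regression, based on the index patient. The text does not say whether the ILI model takes in all index persons or only those with an ILI at home.

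Two other places bear on who falls into the 24%. Section 3.3, under target behaviours, says: "The intervention will encourage the use of regular handwashing throughout the winter months", and extends this to settings outside the family. Under the primary outcome, sections 3.9 and 3.10 say: "We hypothesize that the intervention will reduce the number of episodes (by reducing transmission) and hence the number of days with symptoms".

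**The concern.** Whether a household has an ILI is known only after randomisation. The year-round part of the intervention is aimed partly at that event, because handwashing outside the home can stop an infection from entering it. The population that was sized is therefore a post-randomisation subset whose make-up may differ by group, while the stated analysis principle keeps everyone as randomised.

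If the analysis keeps everyone, the quoted 80% is the power of a different comparison. If it is limited to ILI households, the quoted power matches, but randomisation no longer protects the comparison once the website affects entry, and every ILI that the website keeps out of a home is left out of the result. ILI transmission is part of the primary outcome, so the denominator needs to be settled before the data are analysed.

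**Working it through.** **Inputs.** All come from section 3.12 and its table, with loss to follow-up from section 3.15: two-sided 5% level and 80% power; rates of 20% and 16% where transmission is possible; share 24% (10% x 2.4); loss 20%. Equal allocation is assumed, because the table gives one N per group.

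**1. Reproduce the plan.** The pooled two-proportion formula without continuity correction is

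n = [1.96 x sqrt(2p(1-p)) + 0.8416 x sqrt(p1(1-p1) + p2(1-p2))]^2 / (p1-p2)^2, where p is the mean of p1 and p2.

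With 0.20 and 0.16, p = 0.18 and n = (1.0649 + 0.4567)^2 / 0.04^2 = 1,447 per group, as stated. The total is 2 x 1,447 / 0.24 / 0.80 = 15,073, against 15,074 stated. The other three dichotomous rows also reproduce (6,039, 2,629 and 906 per group). The arithmetic is sound, and it shows that the 80% applies inside the 24%.

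**2. Power inside the subset.** At 16,000 the subset has 16,000 x 0.80 x 0.24 / 2 = 1,536 per group, and power is 82.3%. At 15,074 it is 80.0%.

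**3. Power for all followed-up index persons, with one 24% for both groups.** A person with no household ILI counts as no transmission.

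- Control: 0.24 x 20% = 4.80%.
- Intervention: 0.24 x 16% = 3.84%.
- Difference: 0.96 points.

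Power is Phi{[0.0096 x sqrt(m) - 1.96 x sqrt(2p(1-p))] / sqrt(p1(1-p1) + p2(1-p2))}, with p = 0.0432 and m followed up per group.

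- At 16,000: m = 6,400; (0.7680 - 0.5635) / 0.2874 = 0.711; power 76.2%.
- At 15,074: m = 6,030; (0.7454 - 0.5635) / 0.2874 = 0.633; power 73.7%.
- For 80%: 7,040 per group, or 2 x 7,040 / 0.80 = 17,600 randomised.

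**4. If the website also lowers the share of households with an ILI.** The documents give no figure for this, so a range is assumed. The intervention rate becomes 0.24 x (1 - r) x 16%, where r is the relative reduction in entry.

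| r | Intervention rate | Power at 15,074 | Power at 16,000 |
|---|---|---|---|
| 0% | 3.84% | 73.7% | 76.2% |
| 2% | 3.76% | 80.3% | 82.6% |
| 5% | 3.65% | 88.2% | 90.0% |
| 10% | 3.46% | 96.0% | 96.9% |

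**The case against.** The strongest reply is that the two difficulties trade off. The 74% and 76% hold only if the website has no effect on ILI entering the home. In that case household ILI is unrelated to allocation, and the restricted comparison is not biased by it. If there is an entry effect, the restricted comparison loses its protection, but the full analysis regains its power, and a 2% relative reduction is enough. This stands. A reader might infer that 80% power is out of reach under intention to treat; the documents do not support that, since they expect fewer episodes.

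Other stronger readings also fail:

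- **That a restricted analysis is planned.** Nothing says so. The main analysis is described as intention to treat, and the exact denominator could be set in the statistical analysis plan. What the protocol does fix is a sample size on a denominator that differs from its stated analysis.
- **That 16,000 rests on this row alone.** The bold target for all respiratory infections (20% vs 18%, 15,098) assumes that the whole cohort can be affected, so the 24% does not enter it.
- **That days of illness share the problem.** The ILI column of that row uses the 24%, but the bold target, 3,314, is in the whole-cohort column.
- **That 24% is too high.** The product 10% x 2.4 is an expected number of cases per household. Under independence the share with any case is 1 - 0.9^2.4 = 22.3%. But people living alone are excluded, which raises the mean household size. If one-person households were 10% to 30% of all households (an assumption), the mean for the rest would be 2.3/0.9 = 2.56 to 2.1/0.7 = 3.0, and the share 23.6% to 27.1%. The direction is uncertain.

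**Conclusion.** The point holds as a mismatch between the stated power and the stated analysis. Under the protocol's own assumption of one 24% in both groups, the intention-to-treat comparison has 76% power at 16,000 and 74% at 15,074, which is 4 to 6 points below the quoted 80%. The 16,000, described as giving leeway, is then 1,600 short of the 17,600 needed. The conclusion rests on 20% vs 16% within ILI households, 20% loss, equal allocation and no effect on entry. With even a small entry effect the shortfall disappears, and the remaining issue is that a comparison within ILI households would not be a randomised one.

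This should be clarified before analysis. It does not show that the trial is too small, that the arithmetic is wrong, or that a biased analysis has been chosen.

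**What to change.** - Define the ILI outcome for every followed-up randomised index person: at least one ILI transmission to or from that person, yes or no, with no household ILI counted as no. Say in the main trial analysis that this is the intention-to-treat denominator, and carry it into the statistical analysis plan.
- Restate section 3.12 in unconditional rates: 4.80% vs 3.84%, with 76% power at 16,000 if ILI entry is unaffected. Give the range if it is affected (about 83% for a 2% relative reduction, 90% for 5%), and keep the 20% vs 16% figures beside it as the source.
- Label any comparison limited to ILI households as secondary and non-randomised.

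**Cost.** Wording only, with no more patients. The downside is a stated power about 6 points lower at 16,000 (82% to 76%) if the website has no effect on ILI entry.
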